## Abstract

**Background:**

Children in mixed dentition are highly at risk for dental caries, which is a major health issue worldwide. Despite their effect in controlling dental caries, using probiotics can be challenging. Therefore, it has been advised to use their inanimate forms, called postbiotics. We hypothesize that postbiotics can enhance the oral immunity.

**Methods:**

The aim of this triple-blind, randomized, placebo-controlled trial is to investigate the effect of postbiotic-toothpaste (*Bifidobacterium animalis subsp. animalis*) on salivary levels of Immunoglobulin A (IgA) and pH in children. Using comparing two means formula to calculate the sample size, for this trial 80 healthy 6- to 12-year-old children during mixed dentition with no cavitated dental caries will be selected by convenience sampling method and randomly allocated to two groups, postbiotic-toothpaste or placebo-toothpaste. Saliva samples will be gathered at baseline and four weeks after the intervention. The level of salivary IgA will be determined by ELISA and salivary pH will be measured using a pH meter. Data will be compared within and between groups using independent t-test and paired t-test, in case of normality, with a *p *< 0.05 as statistically significant.

**Discussion:**

If postbiotics-toothpaste prove to be effective in improving the oral immunity, they can be used to prevent dental caries and other oral diseases. The result of this study can help researchers who are working on the immunomodulatory effects of postbiotics in children.

**Trial registration number:**

Iranian Registry of Clinical Trials (IRCT), IRCT20191016045128N2. Registered on 7 March 2022.

## Background

### Background and rationale

Dental caries, the most prevalent oral disease, is still a major health issue worldwide (1). This multifactorial dynamic disease results in mineral loss of dental structure, is dental-biofilm-mediated, and can be modulated by diet (2). In children, it can affect their mastication function, alongside their smile and manner of speaking, and can be a significant blow to their oral health-related quality of life (3).

Children in mixed dentition, which usually begins at six years of age with the eruption of the first permanent tooth and continues until the exfoliation of the last primary tooth at around 12 years of age, are highly at risk for dental caries (4). This is mainly because teeth are most prone to caries in the first 2–4 years of eruption (5). Moreover, erupting teeth are out of alignment with their adjacent teeth and the gingiva in mixed dentition is sensitive and tender, making dental hygiene a challenge for children and their parents (4).

Contrary to the common belief that the rate of dental caries has declined in industrialized countries, this disease is still highly prevalent in these countries (6). It is believed that in European countries, 61% of 6- to 12-year-old children have experienced dental caries (7). A systematic review recently pointed out that the prevalence of dental caries has increased over the past few years in countries from the Middle East and North Africa region (6). So, it is evident that there is a great need for preventive interventions to decrease caries prevalence in children worldwide.

A rather novel preventive method is the usage of probiotics, which seems to be quite effective in controlling dental caries (8). Probiotics are “live microorganisms that confer a health benefit on the host when administered in adequate amounts” (9). Throughout the years, several studies have evaluated the effects of probiotics on oral health and stated that probiotics can reduce the numbers of pathogenic microorganisms, replace them (10, 11), and prevent or treat oral candidiasis, periodontitis, gingivitis, and halitosis (12, 13). Additionally, previous studies indicated the capability of probiotics to enhance the oral immune system and increase salivary Immunoglobulin A (IgA) secretion (14, 15).

Salivary IgA is an antimicrobial protein that is the first immune defense against *Streptococcus mutans*, the primary cariogenic bacteria. It inhibits bacterial adherence and reduces their colonization (16). A recent systematic review showed that, salivary IgA can have protective effects against dental caries (17).

Withal, it has recently been brought to attention that despite the aforementioned health benefits of probiotics, their usage can be quite challenging. Probiotics viability, storage stability, unfavorable effects in immunocompromised patients, antibiotic resistance, and transmission potential are a few of the issues (18, 19). To confront the side effects of probiotics, the usage of their inanimate form, also known as postbiotics, is increasingly gaining interest. According to the recent consensus statement of the International Scientific Association of Probiotics and Prebiotics (ISAPP), postbiotics are “preparation of inanimate microorganisms and/or their components that confers a health benefit on the host” (20). They have been shown to have an inhibitory influence on biofilm formation and alveolar bone loss (19), as well as antibacterial, antiviral, and antioxidant activities (18). Few studies, however, have evaluated the efficacy of postbiotics in enhancing oral immunity.

All in all, there seems to be a lack of enough data to fully support the hypothesis that postbiotics can elevate the salivary IgA concentration. In this protocol, a four-week triple-blind, placebo-controlled, randomized trial, investigating the effects of postbiotics on salivary IgA concentration in 6- to 12-year-old children is reported in detail.

### Objectives

In a study of 80 children, we aim to investigate if daily usage of postbiotic-toothpaste for 30 days can affect salivary levels of IgA in healthy 6- to 12-year-old children. Our secondary aim is to examine the impact of the intervention on salivary pH levels of the children. We hypothesize that daily usage of the postbiotic-toothpaste can elevate the salivary IgA concentration and improve oral immunity.

### Trial design

This will be a four-week, single-center, institutional-based, triple-blind, parallel, placebo-controlled, randomized clinical trial with a convenience sampling technique. Figure 1 shows the flow diagram of the study design from screening the patients to follow-up. This protocol is written according to the SPIRIT 2013 statement (21).

**Figure 1 F1:**
[figure not shown]
Study design flow diagram.

## Methods

### Study setting

The outpatients presenting to the Department of Pediatric Dentistry, School of Dentistry, Ahvaz Jundishapur University of Medical Sciences, Ahvaz, Iran will be recruited.

### Eligibility criteria

The inclusion criteria will be as followed: healthy, 6- to 12-year-old children, during the mixed dentition, no active or untreated carious lesions, no severe crowding, no marked inflammation in oral cavity.

The exclusion criteria will be the presence of any inflammatory disease and use of any medications, supplements, or probiotic intake within the last two weeks or during the intervention. The patients who fail to follow-up will also be excluded from the study.

### Study product and intervention

The postbiotic strain *Bifidobacterium animalis subsp. animalis* PTCC1631 will be used. The intervention will be in form of a postbiotic-toothpaste (*B. animalis subsp. animalis, 10*^*9*^^*CFU*^/*g* (22)). The postbiotic strain was ordered from the Persian Type Culture Collection center, a subset of the Iranian Research Organization for Science and Technology. The postbiotic and placebo-toothpaste are similar in packaging, color, taste, and scent, and the only difference is the absence of the postbiotic ingredient in the placebo-toothpaste. Table 1 shows the ingredients of the toothpastes.

**Table 1 T1:** List of the ingredients of each toothpaste.

	Postbiotic-toothpaste (100 gr)	Placebo-toothpaste (100 gr)
*B. animalis subsp. animalis*	1–5 gr	
Sorbitol	30–40 gr	30–40 gr
Glycerin	20–30 gr	20–30 gr
Calcium carbonate	15–25	15–25
Carboxy methyl cellulose	1–2 gr	1–2 gr
Sodium saccharin	0.1–0.5 gr	0.1–0.5 gr
Sodium lauryl ether sulfate	2–5 gr	2–5 gr
Strawberry flavor	1–2 gr	1–2 gr
Distilled water	qs to 21 ml	qs to 21 ml

Eligible participants will be randomly allocated to two groups, intervention and control. The postbiotic-toothpaste will be given to the children in the intervention group and the children in the control group will receive the placebo-toothpaste. Children in both groups will be asked to brush their teeth twice a day (in the morning and at night) for two minutes, under the supervision of their parents, for four weeks. To eliminate any possible confounding effect of the method of tooth-brushing on the results, children and their parents will be instructed on how, when, and how long to brush their teeth at the beginning of the study.

In order to ensure participants adherence, parents will receive a message on a weekly basis to remind them the importance of tooth-brushing twice a day. Also, to motivate and encourage the children, they will be asked to record daily short videos of themselves while brushing their teeth and put it all together at the end of the four weeks.

### Outcomes

The primary outcome of this study will be the salivary IgA levels of the children and will be reported in mg/100ml. The secondary outcome will be the pH levels of saliva in children. The primary and secondary outcomes will be assessed at the baseline, before any intervention, and after four weeks of intervention.

### Sample size

To calculate the sample size, we used the following comparing two means formula (α=0.05, significance; $\beta \;=\;0.1;{\bar{x}}_{1}\;=\;1.4,\;{\bar{x}}_{2}\;\;=\;\;-3.1,S_{1}\;\;=\;\;4.1,\;\text{and}\;S_{2}\;\;=\;\;5.9$) based on the available literature (23) with maximum 30% falls during the follow-up, the final sample size was 40 participants per arm, 80 in total.

n=(Z(1−β)+Z(1−α/α22))2(S12+S22)(x¯1−x¯2)2

The participants will be selected using the convenience non probability sampling method. So, from the beginning of the study, any patient who meets the inclusion criteria and does not have the exclusion criteria will be selected and this process will continue until the sample size is reached.

### Randomization and blinding

To limit the potential confounding effect of the age of the children, they will be randomly allocated to two groups. Participants will be randomized according to the method of block randomization in blocks of six using a computer-generated random number sequence. This process will be done by an independent statistician who will also give the sealed envelope of the treatment codes to the pharmacist in charge of the production of toothpastes. Each of the eligible patients accepted into the study will be assigned a number from a consecutive range. This number will then be sent to the pharmacist.

During the study, the participants, the outcome assessor, and the data analyst will be blinded and will not have access to the nature of the toothpaste the subjects will be testing. The product will be divided into opaque sealed bags and the labels will not show the difference between the postbiotic and the placebo toothpastes. In case of a serious and adverse event, the blind will be broken and the pharmacist will have access to the sealed envelopes.

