### Data collection

At the beginning of the study, demographic information (age and gender), medical history, accompanying medication, and any usage of antibiotics and probiotics will be recorded. The eligible subjects will be told not to eat or drink anything for one hour before the saliva collection. Afterwards, one ml of the unstimulated whole saliva of children will be collected into sterilized plastic test tubes using the spitting method between 9.00 and 12.00 a.m. under controlled temperature (23°C). The saliva samples will be kept at −80°C until they are sent to laboratory, where the levels of salivary IgA will be determined with enzyme-linked immunosorbent assay (ELISA) previously described in detail by Sonesson et al. (24). The 96 well-plates will be coated overnight by anti-human *α*-chain-specific IgA. The next day, the wells will be washed with Phosphate-Buffered Saline (PBS) containing 0.05% Tween-20 and blocked by 1% Bovine Serum Albumin (BSA) at 37°C for 1 h. Diluted saliva samples and standards will be incubated in wells for 1 h at 37°C. The wells will be washed and biotinylated anti-human IgA antibody will be added. After washing away unbound biotinylated antibody, HRP-conjugated streptavidin will be pipetted to the wells. The wells will again be washed, a TMB substrate solution will be added to the wells and color develops in proportion to the amount of IgA bound. The Stop Solution will change the color from blue to yellow, and the intensity of the color will be measured at 450 nm. The results will be plotted against a standard curve and multiplied with the dilution factor. Immediately after sample collection in order to prevent degradation of the saliva, pH analysis will be carried out using portable pH meter (Hanna Instruments®, HI98191, RI, United States) which will be calibrated with distilled water for each time of use. At the follow-up session, outcomes will be reevaluated accordingly. A trained pediatric dentist will collect all the data. Figure 2 presents schedule of enrolment, intervention, and assessments.

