### Statistical analysis

The analysis of the data will be based on the intention-to-treat analysis and all recruited participants will be considered. Data normality will be examined using the Kolmogorov-Smirnov test. The variables will be reported as mean ± SD or median. The percentage changes for each variable will be calculated using the following formula in which *E* and *B* stand for the end value and the baseline value of the variable, respectively.

$$\left[\;\frac{E-B}{B\;\times \;100}\;\right]$$

In case of meeting the assumption of normality, the significant changes between the two groups will be evaluated using the independent t-test, otherwise, Mann-Whitney analysis will be used. Comparison of the mean of variables at baseline with that of post-intervention within each group will be conducted using paired *t*-test or Wilcoxon signed-rank test. In order to control any possible confounding variable, the analysis of covariance (ANCOVA) will be used when necessary.

All analyses will be performed using the Statistical Package for Social Sciences, version 22.0 (SPSS, Inc., Chicago, IL, United States) with statistical significance at *p *< 0.05.

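### Age is named as a potential confounder, but the between-arm test is unadjusted and adjustment is left to an undefined, data-dependent choice

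*Protocol article*

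**What the plan says.** - **Design.** Randomization and blinding in the Protocol article gives a purpose, "To limit the potential confounding effect of the age of the children, they will be randomly allocated to two groups", and a method: "Participants will be randomized according to the method of block randomization in blocks of six using a computer-generated random number sequence". What goes to the pharmacist is the child's consecutive number. No stratification factor is named.
- **Age range and data.** Eligible children are "healthy, 6- to 12-year-old children, during the mixed dentition". Age is recorded at baseline: "demographic information (age and gender), medical history, accompanying medication". IgA and pH are both measured at baseline and at four weeks (Outcomes).
- **Analysis.** Statistical analysis compares the arms by an independent t-test, or by Mann-Whitney if normality fails. Adjustment appears in one sentence: "In order to control any possible confounding variable, the analysis of covariance (ANCOVA) will be used when necessary". The article lists no covariates and does not say what would make adjustment necessary.

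**The concern.** The plan identifies age as a factor that could distort the comparison, but neither the allocation scheme as described nor the fixed analysis treats age specifically. Blocks of six keep the arm sizes equal; they do not act on age. In a trial of 80, some chance difference in age is likely.

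Whether to adjust for it is left open, and the natural moment to decide is after the baseline table, or the result, has been seen. Two things are at stake: the precision lost by not adjusting for a prognostic covariate, and the extra false-positive risk when two analyses are available and no rule fixes which one counts.

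**Working it through.** **Trial size.** The plan's formula with its own inputs (α = 0.05 two-sided, β = 0.1, means 1.4 and −3.1, SDs 4.1 and 5.9) gives n = (1.2816 + 1.9600)² × (4.1² + 5.9²) / 4.5² = 10.51 × 51.62 / 20.25 = 26.8, so 27 per arm. Then 27/0.70 = 38.6, so 39, against the stated 40. The stated size is reproduced within rounding. I use 40 per arm, and 28 per arm (40 × 0.70) after the maximum loss.

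**Assumptions not in the article.** Ages are uniform over 6 to under 13 years (SD = 7/√12 = 2.02) or, alternatively, clustered around 9 with SD 1.5. The age-outcome correlation ρ is 0.2, 0.3 or 0.5. There is no treatment effect.

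**Size of chance imbalance.** The SE of the difference in mean age is 2.02 × √(2/40) = 0.45 year, so a gap of at least 0.5 year has z = 0.5/0.452 = 1.11 and probability about 27%. With clustered ages it is about 13%. With 28 per arm the SE is 2.02 × √(2/28) = 0.54 year and the probability about 36%. The average difference is zero in every case.

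**Effect of a 0.5-year gap on the outcome.** 0.5/2.02 = 0.25 SD of age. Multiplied by ρ, the outcome shifts by 0.05, 0.07 or 0.12 SD. The design effect is 4.5/√(51.62/2) = 4.5/5.08 = 0.89 SD, so the shift is about 6%, 8% or 14% of it.

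**Error rates and precision.** Simulation of unstratified blocks of six, 80 children, uniform ages, 200,000 trials per correlation:

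| Rate under no effect | ρ = 0.2 | ρ = 0.3 | ρ = 0.5 |
|---|---|---|---|
| Unadjusted t-test, all trials | 5.0% | 5.1% | 5.0% |
| ANCOVA on age, all trials | 5.0% | 5.0% | 5.0% |
| Either one significant | 6.0% | 6.4% | 7.4% |
| Unadjusted, trials with gap ≥ 0.5 year | 5.8% | 6.9% | 9.9% |
| ANCOVA, trials with gap ≥ 0.5 year | 5.0% | 5.1% | 5.0% |
| SE of effect, unadjusted (outcome SD units) | 0.224 | 0.224 | 0.224 |
| SE of effect, age-adjusted | 0.221 | 0.215 | 0.195 |

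The third row follows because the two test statistics correlate at about √(1 − ρ²), that is 0.98, 0.95 and 0.87, so they sometimes disagree. It hardly depends on the age spread (6.1%, 6.4% and 7.2% with clustered ages) or on dropout (6.0%, 6.4% and 7.4% with 56 children).

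Adjusting for age multiplies the variance by about 1 − ρ² = 0.96, 0.91 or 0.75. That is worth roughly 4%, 10% or 33% more children (1/0.96, 1/0.91, 1/0.75). The gain from the baseline value comes on top, but the article gives no figure from which to size it.

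**The case against.** The strongest reply is that the design is sound as written. Random allocation makes treatment independent of age. The article claims only to limit confounding, not to balance age, and the ordinary standard error already covers chance imbalance. All of that stands. A reader might infer that the randomisation sentence is false, that its protection is absent, or that the unadjusted comparison is invalid. The article does not support any of these: the estimate is unbiased and the average error is 5%. Leaving out stratification is not an error either.

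Four further points carry some weight.

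- **No age-IgA association is given.** If it is weak, the effect is small, and a 0.5-year gap moves the outcome by only 6% to 14% of the design effect over the range assumed. This stands; the figures are a range, not a prediction.
- **If changes from baseline are compared, stable age-related differences partly cancel.** This also stands. The relevant ρ is then that between age and change, which may lie at the low end.
- **The data analyst is blinded.** This limits steering towards the postbiotic arm. It does not prevent choosing the smaller p-value, which needs no knowledge of the codes.
- **Covariates are often left to an analysis plan, which is not shown.** The missing covariate list is therefore not the point. The point is what the article does fix: an unadjusted between-arm test, with adjustment conditional on an undefined need. If an analysis plan already settles this, the article need only agree with it.

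**Conclusion.** The point holds as a modest weakness in the analysis, not as a fault in the randomisation. The plan names age as a potential confounder and then leaves adjustment for it to a data-dependent choice.

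The cost is some loss of precision and, in the worst case that the wording allows (reporting whichever of the two analyses is more favourable), a false-positive rate of about 6 to 7.5% instead of 5%. In the roughly 27% of trials with an age gap of at least half a year, the unadjusted rate is about 6 to 10%, against about 5% with adjustment. These figures rest on assumed age-outcome correlations of 0.2 to 0.5 and, for the 27%, on uniformly spread ages. The 6 to 7.5% counts age as the only optional covariate; the wording admits others, which I have not sized.

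**What to change.** In Statistical analysis, replace the conditional ANCOVA sentence with a fixed primary between-arm analysis: ANCOVA of week-4 salivary IgA on arm, baseline IgA and age, and the same model for week-4 pH with baseline pH. Report the unadjusted test as a sensitivity analysis. State the scale on which IgA enters the model at the same time, since the current plan switches tests on a normality check.

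This needs no extra children, visits or assays. Age and both baseline values are already recorded, and the model spends two further degrees of freedom (80 − 4 = 76 instead of 80 − 2 = 78).

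If enrolment is still open, separate block lists by age band are an optional refinement. Two bands cut the SD of the mean-age difference from about 0.45 to 0.24 year. The cost is a second list, the age band sent with the participant number, and arm sizes that may differ by a few children. It does not replace adjustment: with stratified blocks and ρ = 0.5, the unadjusted t-test rejected in only 2.9% of null trials, against 4.8% for ANCOVA, so the gain is lost unless the analysis uses age. The sentence on age in Randomization and blinding can stay.

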### Data collection

At the beginning of the study, demographic information (age and gender), medical history, accompanying medication, and any usage of antibiotics and probiotics will be recorded. The eligible subjects will be told not to eat or drink anything for one hour before the saliva collection. Afterwards, one ml of the unstimulated whole saliva of children will be collected into sterilized plastic test tubes using the spitting method between 9.00 and 12.00 a.m. under controlled temperature (23°C). The saliva samples will be kept at −80°C until they are sent to laboratory, where the levels of salivary IgA will be determined with enzyme-linked immunosorbent assay (ELISA) previously described in detail by Sonesson et al. (24). The 96 well-plates will be coated overnight by anti-human *α*-chain-specific IgA. The next day, the wells will be washed with Phosphate-Buffered Saline (PBS) containing 0.05% Tween-20 and blocked by 1% Bovine Serum Albumin (BSA) at 37°C for 1 h. Diluted saliva samples and standards will be incubated in wells for 1 h at 37°C. The wells will be washed and biotinylated anti-human IgA antibody will be added. After washing away unbound biotinylated antibody, HRP-conjugated streptavidin will be pipetted to the wells. The wells will again be washed, a TMB substrate solution will be added to the wells and color develops in proportion to the amount of IgA bound. The Stop Solution will change the color from blue to yellow, and the intensity of the color will be measured at 450 nm. The results will be plotted against a standard curve and multiplied with the dilution factor. Immediately after sample collection in order to prevent degradation of the saliva, pH analysis will be carried out using portable pH meter (Hanna Instruments®, HI98191, RI, United States) which will be calibrated with distilled water for each time of use. At the follow-up session, outcomes will be reevaluated accordingly. A trained pediatric dentist will collect all the data. Figure 2 presents schedule of enrolment, intervention, and assessments.

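### As worded, calibrating the pH meter with distilled water cannot set its offset or slope; the step for the only secondary outcome should be corrected

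*Protocol article*

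**What the plan says.** The Outcomes section names one secondary outcome: "The secondary outcome will be the pH levels of saliva in children". Both outcomes "will be assessed at the baseline, before any intervention, and after four weeks of intervention".

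The Data collection section gives the method. Directly after the saliva is collected, "pH analysis will be carried out using portable pH meter", and the meter is one "which will be calibrated with distilled water for each time of use". For the second visit it adds only "At the follow-up session, outcomes will be reevaluated accordingly", so the same step governs both time points. No pH reference buffer, second calibration point or check reading appears anywhere in the article.

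The Statistical analysis section plans three uses of the readings: "the significant changes between the two groups will be evaluated using the independent t-test" (or its rank-based alternative), paired tests within each group, and percentage change from baseline.

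**The concern.** Calibrating a pH meter means tying its reading to liquids of known, stable pH. One such liquid fixes the offset; at least two are needed to fix the slope. Distilled water is neither buffered nor assigned a pH value, and it drifts as it takes up carbon dioxide from the air. It is suitable for rinsing an electrode, not for setting one.

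The article states this step as the procedure. It is not a detail left to a fuller document, and a data collector who follows it would have no reference point for any pH value in the trial. The loss could not be repaired afterwards. pH is read on fresh saliva because the authors want to avoid degradation, so by their own reasoning the frozen aliquots are no substitute, and no analysis can recover an offset or slope that was never set or logged.

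**Working it through.** The protocol gives no figure for pH, so there is nothing to reproduce. The check compares the two assays and then traces how a calibration error passes through the planned analyses.

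**The two assays side by side.** In the same section, IgA is read against standards: "The results will be plotted against a standard curve and multiplied with the dilution factor". For pH the only reference named is distilled water.

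**How the error propagates.** Write a reading as *a* + *s*·*x*, where *x* is the true pH, *a* the offset at that use and *s* the slope (a correctly calibrated meter has *a* = 0 and *s* = 1). With baseline B and end value E:

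- Absolute values: both *a* and *s* enter directly.
- Change: (*a*₂ − *a*₁) + *s*(E − B). A constant offset cancels; an offset that differs between the two visits does not.
- Between-arm difference in mean change: *s* times the true difference, plus any imbalance in offsets. Offsets shared by children of both arms at the same visit cancel. Offsets independent of arm add noise but no systematic bias.
- Within-group mean change: a drift common to the second visits is added in full.
- Percentage change: even a constant offset stays in the denominator, because with *s* = 1 the ratio is (E − B)/(B + *a*).

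**Illustration only.** Inputs from the document: "the final sample size was 40 participants per arm, 80 in total". Inputs assumed, not in the document: true difference in pH change 0.3, SD of true change 0.4, and independent error of SD σ in each reading. Then

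- SD of observed change = √(0.4² + 2σ²)
- SE of the difference = SD × √(2/40)

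| σ | SD of change | SE | 0.3/SE | Power (simulated t-test, 4,000 runs) |
|---|---|---|---|---|
| 0 | 0.400 | 0.089 | 3.35 | 91% |
| 0.1 | 0.424 | 0.095 | 3.16 | 88% |
| 0.2 | 0.490 | 0.110 | 2.74 | 78% |
| 0.3 | 0.583 | 0.130 | 2.30 | 62% |
| 0.5 | 0.812 | 0.182 | 1.65 | 37% |

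The normal approximation, Φ(0.3/SE − 1.96), agrees with each simulated figure to within about one percentage point.

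- Slope error of 10% (*s* = 0.9): the estimated difference becomes 0.9 × 0.30 = 0.27.
- Drift in the paired test: with the same SD of change and 40 children, a common shift of 2.02 × 0.4/√40 = 0.13 pH is enough to reach p < 0.05 with no true change.

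The table treats every reading as having its own error. If several children from both arms are read under one calibration, part of that error is shared and cancels, and the loss of power is smaller. The document does not say whether a time of use means a session or a single reading.

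**The case against.** The strongest reply is that one clause in a condensed article is being read too literally. The authors may have meant rinsing the electrode with distilled water, with a buffer calibration they did not report. The text does not exclude that, so it is not established that the readings will be uncalibrated. This stands, and it limits the claim to the wording. It does not rescue the wording, which names distilled water as what the meter is calibrated with and names nothing else.

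The second reply is that the damage is bounded. Allocation is randomised, and participants, outcome assessor and analyst are blinded (Randomization and blinding), so the error falls on both arms alike. Recruitment continues until the target is reached (Sample size). If that takes longer than four weeks, baseline and final readings of different children overlap in calendar time, and random session offsets would tend to average out of the within-group tests; only a systematic drift would look like an effect. The within-group test is not the randomised comparison in any case. All of this stands.

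The third reply is that every figure for the size of the effect rests on assumed inputs. That also stands, and the figures above should be read only as showing the direction and the possible scale.

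**Conclusion.** The sentence is wrong as written and should be corrected. Followed literally, it makes absolute salivary pH unreliable, costs precision in the between-arm comparison, lets a slope error rescale any difference, and exposes the paired tests and percentage changes to drift between visits. These conclusions need only the general fact that unbuffered water has no assigned pH and is at most a single point. Their size cannot be obtained from the document, which gives no SD for pH and no measurement error.

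A reader might infer three stronger things that the document does not support:

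- That the whole secondary outcome rests on an uncalibrated instrument. The clause may be a misworded rinse, and a separate buffer step is not ruled out.
- That the readings are off by a known amount. A figure of up to 1.5 units, for example, follows only if distilled water is assumed to read between 5.5 and 7 and to be taken as 7 (7 − 5.5 = 1.5). The document does not support that assumption or say how the meter would treat such a sample.
- That the trial's main conclusion is at risk. IgA is measured by a separate assay with its own standards, and the pH error does not systematically favour an arm.

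The point is therefore a worthwhile correction to one secondary outcome, not a reason to hold the trial.

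**What to change.** Replace the clause with wording such as: *calibrated before each session against at least two certified pH reference buffers that together span the expected salivary range on both sides of pH 7, with a buffer check reading logged before samples are read and at the end of the session; distilled water is used only to rinse the electrode between samples.*

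Add two rules, with a tolerance that the trial team sets in advance:

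- If the opening check fails, recalibrate before any sample is read.
- If the closing check fails, keep that session's readings, flag them, and repeat the pH analysis without them as a sensitivity analysis. Repeating the readings is not possible, because pH is read on fresh saliva.

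The buffers must cover both sides of pH 7 between them; a set that stops near 7 leaves part of the range outside the calibrated interval.

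If buffers are already in use, the change amounts to correcting the sentence and logging the checks. Otherwise the cost is buffer solutions and a few minutes per session. Sample size, visits and the IgA procedure are unaffected.
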